#### Analyses

Interviews in (A) are analyzed through the qualitative analysis approach according to Kuckartz [31]. In (B), the interviews are analyzed through the qualitative analysis approach according to Mayring [32]. Mayring's model is more theory-driven and thus more suitable for analyzing the upstream interviews, which are intended to help conceptualize the content of the focus groups, from our perspective. SOFGs are analyzed in two steps. First, aspects and experiences of the participants on a specific input are collected, discussed, and defined on moderation cards. Subsequently, the "codes" are categorized according to the principles of the Concept Mapping Approach [33–35] during the meeting. In this way, interpretation errors can be reduced. The discussions are video-recorded and transcribed. In the second step, the final transcripts will be analyzed using MAXQDA according to the framework approach [36] by two independent researchers. AOFGs are analyzed as described in the second step.

### Project timeline

The AVENIR project started in August 2022. To date (November 2023), the preparation phase is completed. This phase included the definition of inclusion criteria, and variables used, as well as the preparation of analysis plans in module 1 and 2. In module 3, literature reviews and upstream interviews informing the interview guidelines and pilot interviews were conducted and recruitment of participants has started. For all three modules, ethics and data protection votes were obtained. We plan for completing data collection and analyses by February 2025, and derivation of patient information and recommendations to improve sepsis care by August 2025.

## Discussion

Given the large number of sepsis patients and their families who have experience mortality and substantial long-term morbidity from sepsis, the improvement of sepsis care is considered a global public health priority [14]. The overarching aim of the AVENIR study is to advance the understanding of current sepsis care practices and patient needs by triangulation of the quantitative analysis of nationwide health claims data and EMS data, with the qualitative perspective from patient, caregiver and health care provider interviews and focus groups. By that, the AVENIR study generates nuanced knowledge on every phase of the care pathway from sepsis onset to long-term care. It will help to understand patients’ perception of optimal care, and providers perceptions of facilitators and challenges of delivering care in this way, particularly at intersectoral transitions. Furthermore, the study helps to identify patient-, sepsis- or treatment related factors during an acute stay associated with adverse outcomes or specific health care utilizations patterns, which may help to design and tailor interventions to support patients beyond their immediate discharge from hospital based on their specific needs. At a health system and policy level, the results may support resource allocation, capacity planning and the implementation of policies that enhance acute and longitudinal sepsis care.

A major strength of the study is its mixed-methods design and the comprehensive database including both primary and secondary data sources. We use health claims data from approximately one third of the German﻿ population, that records health care utilization in most German health care sectors (inpatient, outpatient, rehabilitation, medical remedies, chronic care). The data linkage of PCR of EMS and health claims data completes the database with data from two federal states and enables the follow-up of short- and long-term outcomes of EMS patients with and without sepsis. This also allows to explore the extent of unrecognized sepsis in EMS care and its impact on sepsis treatment and outcomes. Beyond the information drawn from health claims data, our study generates an immersion into the perspectives and needs of patients, family members, and providers.

Our study has also limitations to consider. On the one hand, these arise from inherent limitations of research using health claims data, such as potentially incomplete, inaccurate, or missing data, and inability to adequately evaluate the appropriateness of care [37, 38]. Although health care utilization and costs can be researched with high validity, recorded incidences of diseases have to be considered as administrative as only diseases diagnosed and coded correctly during hospitalizations and outpatients visits can be detected. For sepsis, we know from previous validation studies that the coding of diagnoses captures cases only with low sensitivity, and misses cases with lower disease severity [39]. This fact may be aggravated by the change in sepsis-related ICD-10-GM codes in 2020 in Germany. We address this issue by applying different case identification strategies for the years 2016–19 and 2020 (Table 1), but still it is likely that our sepsis definition does not capture all sepsis patients treated in German hospitals.

In module 2, exclusively PCR of EMS from study regions in Bayern and Baden-Württemberg as well as from selected EMS organizations will be processed. Hence, all generalizations of study results with regard to these two federal states or to the entire health care system in Germany must be examined carefully.

Furthermore, undesired selection effects may be introduced into the database in case key variables needed for the linkage of PCR and health claims data are unavailable selectively (e.g. KVNR). However, it is known from previous studies [22] that data linkage with health claims data is possible even if the key variable KVNR is not available for some of the PCR.

Qualitative data curation in module 3 might be limited by the fact that since participants of the oral interviews are not sharing statements anonymously in interviews and SOFGs, statements might not be free from social desirability effects. The sample might be subject to self-selection bias as participation will be voluntarily. Moreover, interviews using a video conference system may not reach the same depth as face-to-face interviews as rapport building can be limited. However, using online video-supported interviews allow for a composition of groups without logistic concerns and geographical restrictions, which increases the groups ‘ diversity and quality.

In conclusion, the results of the mixed-method study AVENIR contribute to a deeper understanding of sepsis care pathways in Germany. In the long-term, this may help to foster improvements and innovations in sepsis care, which can contribute to reduce the immense personal, medical, and societal burden of sepsis and its sepsis sequelae.

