**Methods:**

Mixed-methods study including (1) analysis of anonymized nationwide health claims data from Germany, (2) linkage of health claims data with patient care reports (PCR) of emergency medical services from study regions in two federal states within Germany, and (3) qualitative exploration of the patient, relative, and care provider perspective on sepsis care. In (1), we analyze inpatient and outpatient health care utilization until 30 days pre-sepsis; clinical sepsis care including intra- and inter-hospital transfers; and rehabilitation, inpatient and outpatient aftercare of sepsis survivors as well as costs for health care utilization until 24 months post-sepsis. We attempt to identify survivor classes with similar health care utilization by Latent Class Analyses. In (2), PCR are linked with health claims data to establish a comprehensive database outlining care pathways for sepsis patients from pre-hospital to follow-up. We investigate e.g., whether correct initial assessment is associated with acute (e.g., same-day lethality) and long-term (e.g., new need for care, long-term mortality) outcomes of patients. We compare the performance of sepsis-specific screening tools such as qSOFA, NEWS-2 or PRESEP in the pre-clinical setting. In (3), semi-structured interviews as well as synchronous and asynchronous online focus groups are conducted and analyzed using qualitative content analyses techniques.

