#### Patient sample

(A) The patient sample includes all EMS cases treated by cooperating EMS organizations in Bayern and Baden-Württemberg between January 1, 2017, and December 31, 2021.

(B) The patient sample consists of individuals for whom a linkage can be established between PCR and health claims data. The health claims data cover the period from January 1, 2016, to December 31, 2022, thereby allowing for a one-year pre- or post-analysis of all patients' EMS-cases. The sample only includes data from individuals with a continuous insurance period or death within observation period.

In module 2, neither PCR nor health claims data are subject to sepsis-specific pre-selection. Consequently, the PCR comprise cases of patients with and without suspected sepsis, and the health claims database consists of patients with and without diagnosed sepsis.

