#### Measurements

(A) The PCR are first examined with regard to their documentation quality. This includes, for example, the frequency of missing values, invalid values or non-plausible values. Checks of vital signs are especially important in this process, since they are often not documented even in case of suspected infection or sepsis [25].

We will investigate the proportion of patients with a documented suspicion of sepsis in the pre-hospital setting and the symptoms of these patients. We analyze what proportion of patients with suspected sepsis already receive care by emergency physicians in the pre-hospital setting, and how the pre-hospital care of sepsis patients with and without the involvement of emergency physicians differs. In addition, we investigate which therapies are initiated in the pre-hospital setting if sepsis is suspected (e.g., drug administration, oxygen administration, ventilation, administration of antibiotics, fluid therapy, catecholamines, vasopressors).

(B) Based on the linked data, we assess in which sectors (e.g. outpatient treatment, inpatient admission to a hospital) of the health care system patients received follow-up care after EMS treatment, and if this care differs with respect to sepsis suspicion during EMS treatment. Further analysis will determine whether sepsis suspicion in the pre-hospital setting affects short- and long-term patient outcomes (e.g., ventilation, mortality, readmission due to specific diagnoses, need for new care).

In addition, sepsis-specific screening tools such as qSOFA and others [26, 27] will be operationalized based on available vital signs in PCR. The aim is to evaluate how precise the pre-clinical screening tools detect sepsis and if this precision changed over time compared to a clinically confirmed and coded sepsis diagnosis (defined in accordance to Module 1) during a subsequent hospitalization.

A special focus lies on false-negative classifications, i.e. patients without a pre-clinical suspicion of sepsis but confirmed sepsis diagnosis in health claims data. For this group, potential sepsis characteristics (e.g. organ dysfunction by qSOFA) or patient characteristics will be investigated in more detail.

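### Module 2 judges EMS sepsis recognition against later hospital coding, which may itself depend on the crew's suspicion; the plan neither acknowledges nor checks this

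*Protocol article*

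**What the plan says.** Module 2, Measurements (B), fixes the reference standard. Screening tools are assessed "compared to a clinically confirmed and coded sepsis diagnosis (defined in accordance to Module 1) during a subsequent hospitalization". Missed sepsis is defined as "patients without a pre-clinical suspicion of sepsis but confirmed sepsis diagnosis in health claims data". So suspicion comes from the PCR, and sepsis status comes from claims data for a hospital stay that follows the EMS contact.

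Three places draw inferences about recognition. The same section asks "whether sepsis suspicion in the pre-hospital setting affects short- and long-term patient outcomes". The Abstract (Methods) asks "whether correct initial assessment is associated with acute (e.g., same-day lethality) and long-term" outcomes; an assessment can be called correct only once a later sepsis status is known. The Discussion says of the linked data: "This also allows to explore the extent of unrecognized sepsis in EMS care and its impact on sepsis treatment and outcomes".

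The limitations in the Discussion state that "the coding of diagnoses captures cases only with low sensitivity, and misses cases with lower disease severity", and that "only diseases diagnosed and coded correctly during hospitalizations and outpatients visits can be detected". They present this as general under-capture, possibly worsened by the 2020 code change. Nothing in the article says that coding could vary with the crew's suspicion.

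**The concern.** The reference standard is established after the index assessment and with possible knowledge of it. A crew that hands over a suspicion of sepsis may prompt the work-up that ends in a sepsis code. By the plan's own account milder sepsis is the kind that coding misses, so that is where a prompt has most room to act. Severe sepsis is more likely to be coded either way.

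If that happens, two results are affected. Suspected cases are over-represented among coded sepsis, so EMS recognition looks more frequent than it is. Coded suspected sepsis also contains relatively more mild cases than coded unsuspected sepsis, which pulls its mortality, ventilation and new care need down even if recognition changes nothing. Limiting the comparison to coded sepsis does not remove this, because the selection happens at coding. The project intends to derive care recommendations, so a coding artefact read as a benefit of recognition would matter.

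**Working it through.** **The plan's own figure.** Module 2, Sample size considerations, expects 22,700 to 45,400 sepsis cases. 2.8 million × 0.40 = 1.12 million; × 0.02 = 22,400; × 0.04 = 44,800. Both are 1.3% below the stated values, so the figure reproduces to rounding. With numbers of this order, sampling error is unlikely to be the main uncertainty.

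**Illustration.** The documents give no coding probabilities by severity or by suspicion, so every input below is an assumption:

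- True sepsis is half severe (mortality 40%) and half mild (10%). Suspicion has no effect on death.
- Unsuspected sepsis is coded in 70% of severe and 20% of mild cases.
- Suspected sepsis is coded in a share k of severe and c of mild cases.
- Crews suspect a share pS of severe and pM of mild cases, 20% overall.

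Coded fractions: suspected severe A = 0.5·pS·k; suspected mild B = 0.5·pM·c; unsuspected severe D = 0.5·(1−pS)·0.70; unsuspected mild E = 0.5·(1−pM)·0.20.

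Mortality in suspected coded sepsis = (0.40A + 0.10B)/(A + B). In unsuspected coded sepsis it is (0.40D + 0.10E)/(D + E). Apparent recognition = (A + B)/(A + B + D + E).

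Worked line (pS = pM = 0.20, k = 0.70, c = 0.40): A = 0.07, B = 0.04, D = 0.28, E = 0.08. Suspected: 0.032/0.11 = 29.1%. Unsuspected: 0.12/0.36 = 33.3%. Ratio 0.873. Recognition: 0.11/0.47 = 23.4%.

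| pS / pM | k | c | Suspected | Unsuspected | Ratio | Apparent recognition |
|---|---|---|---|---|---|---|
| 20% / 20% | 70% | 20% | 33.3% | 33.3% | 1.000 | 20.0% |
| 20% / 20% | 70% | 30% | 31.0% | 33.3% | 0.930 | 21.7% |
| 20% / 20% | 70% | 40% | 29.1% | 33.3% | 0.873 | 23.4% |
| 20% / 20% | 70% | 50% | 27.5% | 33.3% | 0.825 | 25.0% |
| 30% / 10% | 70% | 20% | 37.4% | 31.9% | 1.171 | 25.6% |
| 30% / 10% | 70% | 30% | 36.3% | 31.9% | 1.135 | 26.4% |
| 30% / 10% | 70% | 40% | 35.2% | 31.9% | 1.102 | 27.2% |
| 30% / 10% | 70% | 50% | 34.2% | 31.9% | 1.072 | 28.0% |
| 20% / 20% | 90% | 25% | 33.5% | 33.3% | 1.004 | 24.2% |
| 20% / 20% | 90% | 30% | 32.5% | 33.3% | 0.975 | 25.0% |

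**Reading the table.**

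- Under-coding of mild sepsis that does not depend on suspicion (first row) produces no spurious contrast when suspicion is unrelated to severity. Dependence on suspicion does.
- When crews suspect severe cases more often, the ratio stays above 1, but each rise in c still lowers it, from 1.171 to 1.072.
- When suspicion also raises coding of severe cases, the ratio can sit near 1. Recognition is still overstated.

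**Second set of assumptions** (mortality 50% and 20%; coding 60% severe, 20% mild unsuspected). With suspicion unrelated to severity and c = 30/40/60%, the mortality difference is −2.5/−4.5/−7.5 points (odds ratio 0.90/0.83/0.73) and apparent recognition 22.0/23.8/27.3%. With 30%/10% suspicion, the difference is +6.0 points at c = 20%, +3.5 at 40% and +1.5 at 60%. The pattern is the same.

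**The case against.** Several points on the other side stand.

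- **Mechanism.** No document shows that EMS suspicion changes hospital coding. It is plausible, and its size is unknown.
- **Direction.** A reader might infer that the study will report lower mortality in suspected sepsis. The documents do not support that. It needs suspicion to be unrelated to severity and severe coding to be unaffected; relaxing either can bring the ratio to 1 or above.
- **Source of the labels.** A reader might also infer that recognition itself is read from hospital codes. It is not: suspicion is documented in the PCR, and only sepsis status is coded.
- **Which contrast is planned.** The outcome question in Measurements (B) is not restricted to coded sepsis, and the false-negative paragraph there is descriptive. The contrast within coded sepsis rests on the Abstract and one exploratory sentence in the Discussion.
- **Disclosure.** Under-coding of milder sepsis is disclosed. With 30%/10% suspicion it alone lifts apparent recognition to 25.6%; dependence on suspicion at c = 40% adds only 1.6 points.
- **Analysis plans.** Project timeline says that plans for Modules 1 and 2 were prepared. Adjustment and sensitivity analyses may be there.

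The last point does not dispose of the matter. The article itself fixes the reference standard, the definition of missed sepsis and the inference. Severity adjustment of outcomes could reduce the outcome bias but would not correct the recognition share, and Measurements (A) notes that vital signs are frequently missing.

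**Conclusion.** The concern holds as an unaddressed bias of known tendency and unknown size. If suspicion raises coding mainly of milder sepsis, the EMS recognition share is biased upwards and the outcome contrast within coded sepsis is shifted towards apparent benefit. In the main illustration, with no true effect and suspicion unrelated to severity, the ratio moves from 1.00 to 0.930–0.825 and recognition from 20% to 21.7–25.0%. These figures show that the effect need not be negligible; they are not estimates. The net sign of the reported contrast is not established, because confounding by severity can outweigh the shift and prompted coding of severe cases can offset it. This is a cheap improvement worth making, not a flaw that invalidates Module 2.

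**What to change.** Keep the coded-sepsis analysis and add the following beside it:

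1. Run the outcome contrast by EMS suspicion in a linked group defined by PCR vital signs, for example a positive result on the screening tools that Module 2 already operationalises, regardless of later coding. As a second version, use admitted cases with any infection code plus organ dysfunction, with or without a sepsis code. The data permit this, since "neither PCR nor health claims data are subject to sepsis-specific pre-selection", and Table 1 already uses such a rule for influenza and Covid-19 in 2020.
2. Report the share of cases that receive a sepsis code, by EMS suspicion, within strata of PCR vital-sign severity.
3. Describe the recognition share as that of hospital-coded sepsis. Do not interpret the coded-sepsis contrast as an impact of recognition if the coding share differs by suspicion or if the groups disagree.
4. Add suspicion-dependent coding to the limitations.

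The cost is one extra code list and repeated runs on data already held. The downsides should be stated. The alternative groups are less specific for sepsis. Missing vital signs will shrink the first group and may select it. Infection and organ-dysfunction codes can also respond to suspicion, which is why the vital-sign group comes first. Equal coding shares would not prove absence of bias.

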## Data Availability

Not applicable to the study protocol presented in this manuscript.

## Abbreviations

AOFG: Asynchronous online focus group
AOK: Statutory health insurance fund, AOK – Die Gesundheitskasse
BW: Baden-Württemberg, federal State
BY: Bayern, Federal State
EMS: Emergency medical services
ICD: International classification of diseases
KVNR: Health insurence number, Krankenversichertennummer
LCA: Latent class analysis
LTA: Latent transition analysis
OPS: German procedure classification, operationen- und prozedurenschlüssel
PCR: Patient care report
PSS: Post sepsis syndrome
SGB: Social code book, sozialgesetzbuch
SOFG: Synchronous online focus group
WIdO: AOK research Institute, Wissenschaftliches Institut der AOK
